### Study setting

The study will be conducted in 8 hematopoietic stem cell transplantation centers in China, including the First Medical Center of Chinese PLA General Hospital; the Fifth Medical Center of Chinese PLA General Hospital; Institute of Hematology & Blood Disease Hospital, Chines Academy of Medical Sciences & Peking Union Medical College; Shandong Provincial Hospital Affiliated to Shandong First Medical University; the Second Hospital of Hebei Medical University; the First Affiliated Hospital of Zhengzhou University; Henan Provincial People’s Hospital; and the Affiliated Hospital of Xuzhou Medical University, which are highly experienced in the management of GVHD and hematopoietic stem cell transplantation with routine patient education about clinical trials.

This study started in June 2020, and patients will be recruited over the course of 2 years. Each study site will use the newly diagnosed aGVHD patient list to identify and recruit potential subjects. Recruitment videos and advertisements for potential subjects will be advertised among patients through their doctors. If a patient intends to enter the study, dedicated staff will meet with the patient face-to-face, give more detail to introduce the study, and arrange the appropriate screening procedures.

### Study endpoints

This trial aims to assess the efficacy and safety of hUC-MSC PLEB001 in patients with grade II–IV steroid-refractory aGVHD. The primary endpoint is the overall response rate (ORR) at day 28, which is defined as the proportion of patients achieving a CR or PR without the use of additional systemic therapies for aGVHD. The secondary endpoints include the CR rate at day 28, ORR at day 56, CR rate at day 56, durable ORR at day 56, DCR, OS, and Eastern Cooperative Oncology Group (ECOG) score. The safety endpoints include adverse events (AEs), serious adverse events (SAEs), and infusion toxicity (Table 2).

**Table 2 Tab2:** Study endpoints

Aim	Indicator
Primary endpoint	ORR at day 28
Secondary endpoints	CR at day 28, day 56
	ORR at day 56
	Durable ORR at day 56
	DCR within day 100
	OS at day 100, day 180
	ECOG score at day 28, day 56, day 100
Safety endpoints	AE/SAE at day 180
	infusion toxicity at day 14

1. Complete remission (CR): absence of any aGVHD-related symptoms

2. Partial remission (PR): an improvement in severity of at least 1 stage in all initial organs without further deterioration of other organs

3. No response (NR): the absence of improvement or deterioration of symptoms in any organ or death

4. Progressive disease (PD): a deterioration in the severity of at least 1 stage in a single organ with or without improvement in other organs

5. Overall response rate (ORR) = CR + PR

6. Durable ORR: the percentage of subjects who achieve CR + PR on day 28 and remain CR + PR on day 56

7. Durable complete response (DCR): complete resolution of aGVHD symptoms for at least 28 days within 100 days after the first infusion

8. Infusion toxicity includes fever, phlebitis, headache, dizziness, nausea, chest pain, shortness of breath, transient pulmonary edema, allergic reaction, skin rash, injection site pruritus, etc.

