## Methods

### Trial design

This is a multicenter, randomized, double-blind, placebo-controlled, superiority, phase II trial (Chinese Clinical Trial Registry, ChiCTR2000035740) that will enroll patients with grade II–IV steroid-refractory aGVHD from 8 Chinese centers. The primary endpoint is the overall response rate (ORR) at day 28. A total of 96 patients will be randomly assigned at a 1:1 ratio to receive either MSCs or placebo in a double-blinded manner. To ensure the interests of the patients, both the MSC and placebo groups will receive conventional second-line therapy. The MSC group will receive an infusion of hUC-MSC PLEB001 at 1.0 × 10^6^ MSC/(kg of subject, adjusted body weight) twice a week for 4 weeks. The control group will receive placebo treatment at the same frequency. The treatment efficacy will be assessed on the 28th day after the first infusion in all patients. The treatment will be terminated if the patient reaches complete response (CR), no response (NR), or progression of disease (PD) on the 28th day. Patients who display PR at day 28 will receive further infusions twice per week for an additional 4 weeks. The total treatment period will last no more than 8 weeks.

The conventional second-line therapy for patients with steroid-refractory aGVHD includes basiliximab, ruxolitinib, mycophenolate mofetil, methotrexate, etc. Investigators from each center will ensure the consistency of indications, category, and administration of second-line therapies. If deterioration or rapid progression of aGVHD is observed, another second-line agent can be added to the trial treatment regimen.

The protocol and the proposed informed consent form (ICF) will be reviewed and approved by an independent ethics committee (EC) before the study starts. Eligible patients may only be enrolled in the study after providing written informed consent.

In addition, peripheral blood samples will be collected from patients for the detection of Treg and Th17 cell populations prior to and after the treatment. Additional consent for peripheral blood sample collection and detection will also be included in the informed consent form.

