Abdominal ultrasound scan^a^		**X**									**X**									**X**				
Th17 and Treg count (prior to MSC infusion)			**X**				**X**				**X**									**X**				
CEA, CA125, CA199, AFP^a^		**X**									**X**									**X**				
X-ray or CT of chest		**X**									**X**									**X**				
Gastrointestinal examination		**X**		**X**	**X**		**X**		**X**		**X**		**X**		**X**		**X**			**X**	**X**	**X**		
Cutaneous examination		**X**		**X**	**X**		**X**		**X**		**X**		**X**		**X**		**X**			**X**	**X**	**X**		
aGVHD evaluation^1^		**X**		**X**	**X**		**X**		**X**		**X**		**X**		**X**		**X**			**X**	**X**	**X**		
ECOG score		**X**									**X**									**X**		**X**		
Pregnancy test( for female of child bearing potential)		**X**									**X**									**X**				
SaO2/SAT^2^		**X**	**X**	**X**	**X**	**X**	**X**	**X**	**X**	**X**		**X**	**X**	**X**	**X**	**X**	**X**	**X**	**X**					
Inclusion/exclusion criteria		**X**																						
Intervention			**X**	**X**	**X**	**X**	**X**	**X**	**X**	**X**		**X**	**X**	**X**	**X**	**X**	**X**	**X**	**X**					
AEs			**X**	**X**	**X**	**X**	**X**	**X**	**X**	**X**	**X**	**X**	**X**	**X**	**X**	**X**	**X**	**X**	**X**	**X**	**X**	**X**	**X**	
Concomitant disease and medication		**X**	**X**	**X**	**X**	**X**	**X**	**X**	**X**	**X**	**X**	**X**	**X**	**X**	**X**	**X**	**X**	**X**	**X**	**X**	**X**	**X**	**X**	
Medical recording of aGVHD after investigational product																					**X**	**X**	**X**	
Imaging of secondary tumors																						**X**	**X**	**X**
Survival status			**X**	**X**	**X**	**X**	**X**	**X**	**X**	**X**	**X**	**X**	**X**	**X**	**X**	**X**	**X**	**X**	**X**	**X**	**X**	**X**	**X**	**X**

Subjects who withdraw from the trial should be assessed according to visit 19

Detailed information about the test items is shown in the clinical trial protocol V6.0, which could be provided by the trial sponsor

1. According to the modified Glucksberg criteria

2. Monitoring with a pulse oximeter at least 30 min before MSC infusion to 2 h after infusion

^a^Test results prior to randomization are acceptable during the screening period, and the exact time limits are described in the clinical trial protocol V6.0

Subjects who deviate from intervention protocols or the follow-up schedule of assessments will follow the same calendar as those with good compliance, except adherence assessment.

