### Safety reporting

#### AE

Adverse events are collected through interrogation, physical examination, laboratory or other tests, and self-reporting. Investigators are required to collect AEs from the time of the first dose and continue to collect AEs until 180 days after the first infusion, death, or early withdrawal from the clinical study (whichever occurs first).

In this trial, the severity of adverse events is graded according to the common terminology criteria adverse events (CTCAE 5.0) published by the National Cancer Institute (NCI) [20]. The potential association between adverse events and investigational product will be examined based on the “Adverse Drug Reaction Reporting and Detection Workbook” issued by the National Adverse Drug Reaction Monitoring Centre.

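### The named infusion-toxicity endpoint is set at day 14, so on its natural reading it counts 4 (at most 5) of the 8 or 16 planned infusions, although later reactions are still captured as adverse events

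*Protocol article*

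**What the plan says.** Table 2 of the protocol article (Study endpoints) has two safety rows: "AE/SAE at day 180" and "infusion toxicity at day 14". Note 8 to that table describes the second by example: "Infusion toxicity includes fever, phlebitis, headache, dizziness, nausea, chest pain" and further acute events, among them allergic reaction and transient pulmonary edema. No section gives infusion toxicity another time point.

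Trial design schedules infusions "twice a week for 4 weeks" and then states: "Patients who display PR at day 28 will receive further infusions twice per week for an additional 4 weeks". It caps the course: "The total treatment period will last no more than 8 weeks". Table 1 marks the Intervention row at Visits 2–9 (days 1, 4, 8, 11, 15, 18, 22, 25) and Visits 11–18 (days 29, 32, 36, 39, 43, 46, 50, 53). After day 1, each of these visits has a window of ±1 day.

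On data collection, the AE section has investigators "continue to collect AEs until 180 days after the first infusion". Table 1 marks adverse events at every infusion visit. Oxygen saturation is also marked at every infusion visit, with this footnote: "Monitoring with a pulse oximeter at least 30 min before MSC infusion to 2 h after infusion".

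**The concern.** The events in note 8 are acute reactions that any infusion can cause. An endpoint meant to describe them should follow the infusions. Every planned course runs past day 14, because the response-based decision to stop or continue is made at day 28. A result labelled infusion toxicity but cut at day 14 would describe only the early part of treatment, and it would describe least of it for patients with partial response, who receive the most infusions. The Discussions section names tolerability and safety as one of the trial's two questions, so a reader could take the day-14 rate as the rate for the whole course.

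The wording is also unclear. With no day-14 visit in Table 1 (the nearest are 11 ± 1 and 15 ± 1), the article does not say whether the endpoint is cumulative to day 14, an assessment made on that day, or a period of 14 days after an infusion.

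**Working it through.** **Inputs.** Infusion frequency and duration come from Trial design, visit days and windows from Table 1, and the time point from Table 2.

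**Step 1: reproduce the number of infusions.**
- Initial course: 2 per week × 4 weeks = 8. Table 1 marks 8 (Visits 2–9).
- With the extension: 2 per week × 8 weeks = 16. Table 1 marks 8 + 8 = 16 (Visits 2–9 and 11–18).

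Text and table agree.

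**Step 2: count infusions on or before day 14**, taking the endpoint as cumulative from the first infusion.

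| Timing within the visit windows | Infusions by day 14 | Share of 8 | Share of 16 |
|---|---|---|---|
| Nominal days (1, 4, 8, 11) | 4 | 4/8 = 50% | 4/16 = 25% |
| One day early (Visit 6 on day 14) | 5 | 5/8 = 62.5% | 5/16 = 31.25% |
| One day late | 4 | 50% | 25% |

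The share left out is therefore 37.5% to 50% of the 8-infusion course and 68.75% to 75% of the 16-infusion course.

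**Step 3: average over patients.** The article does not give the share of patients who continue after day 28, so treat it as an assumption q. With full courses and nominal days, the share of all planned infusions left out is 1 − 4/(8 + 8q):
- q = 0: 1 − 4/8 = 50%
- q = 0.25: 1 − 4/10 = 60%
- q = 0.5: 1 − 4/12 = 67%
- q = 1: 1 − 4/16 = 75%

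**Step 4: effect on a per-subject rate (illustration only).** The documents give no per-infusion risk. Assume a risk p that is constant and independent across infusions. The share of patients with at least one reaction in n infusions is 1 − (1 − p)^n:

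| Assumed p | First 4 infusions | 8 infusions | 16 infusions |
|---|---|---|---|
| 1% | 3.9% | 7.7% | 14.9% |
| 2% | 7.8% | 14.9% | 27.6% |
| 5% | 18.5% | 33.7% | 56.0% |

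Over this range the four-infusion figure is about half the 8-infusion figure and about a quarter to a third of the 16-infusion figure. If reactions cluster in the same patients or mostly occur at the first infusions, the loss is smaller. If risk rises with repeated exposure, it is larger. The documents do not say which applies.

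**Step 5: the other readings of day 14.** An assessment made only on that day would cover no more than the cumulative reading. A period of 14 days after each infusion would cover every infusion, but nothing in the article states it. The adverse-event period and the durable complete response definition both count from the first infusion, which favours the cumulative reading.

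**The case against.** **Later reactions are already in a safety endpoint.** This stands. An allergic reaction at the seventh or fourteenth infusion is an adverse event. It is graded by CTCAE 5.0, assessed for relation to the product, and tabulated under the day-180 endpoint. A reader might infer that reactions after day 14 escape the safety evaluation, but the documents do not support that. What remains is that the article does not say the general table will separate infusion reactions or relate them to the number of infusions given, which is the purpose of a dedicated endpoint.

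**The endpoint need not miss half of the course.** This also stands. A reader might infer that at most half of the initial course is covered, but with Visit 6 on day 14 it is 5/8.

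**Re-exposure is not excluded.** Infusions 2 to 4 are themselves re-exposures inside the window, and the documents report no risk that rises with repetition. An argument from late sensitisation would be speculation here.

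**A fixed early window keeps planned exposure equal between arms.** This is the best argument for an early cut. The extension depends on response, so a per-subject rate to day 53 would compare arms with different exposure if partial-response rates differ. It argues against day 53 for the between-arm comparison, but it does not favour day 14 over the whole initial course, which is also planned identically in both arms.

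**The full protocol or the analysis plan may define the window.** Event windows and denominators may well be there, and their absence from the article is not the point. The day-14 time point is stated in the article itself, and it does not fit the infusion schedule stated beside it.

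**Conclusion.** The point holds, limited to the definition of one named safety endpoint. On the cumulative reading it counts 4 infusions, or 5 at the edge of the visit window: 50% to 62.5% of the 8-infusion course and 25% to 31% of the 16-infusion course. The conclusion rests on two assumptions: that day 14 is counted from the first infusion, as other times in the article are, and that infusions follow the Table 1 windows. It does not rest on any assumed per-infusion risk. The data needed for a complete endpoint are already collected, so this is a mismatch of definition that should be corrected; it is not a failure of safety monitoring.

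**What to change.** In Table 2, replace the day-14 time point with a definition tied to the infusions: the listed events starting within a fixed window after each infusion, for all infusions given. State the window length. Then report:

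1. **Between-arm comparison:** the per-subject rate over the initial course common to all patients (through day 28). Defining this as infusions 1 to 8 avoids an edge case, since Visit 11 (29 ± 1) can fall on day 28.
2. **Per-infusion rate:** through the last infusion, with infusions given as the denominator. Show the extension separately, because entry depends on response and exposure may differ by arm.
3. **Day 14:** a supportive cut only, stated as cumulative from the first infusion.

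The cost is a change to Table 2, matching analysis wording and a few more tables. Adverse events and oximetry are already marked at every infusion visit, so no new visits are needed. The reported rate would be expected to be higher than the day-14 figure and should be presented with its longer period of exposure. The change should be made before unblinding, and dosing, schedule and patient management stay as they are.

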### Study population

The target population will be patients suffering grade II–IV steroid-refractory aGVHD.

The inclusion criteria are as follows:i.Male or female aged between 13 and 70 yearsii.Patients with malignant hematologic diseases who received their first allogeneic hematopoietic stem cell transplantation and developed grade II–IV steroid-refractory aGVHD. AGVHD may develop after donor lymphocyte infusion

First-line glucocorticoid therapy refers to methylprednisolone 1 mg/kg/day or 2 mg/kg/day or an equivalent dose of steroids.

Steroid-refractory aGVHD is defined as patients administered first-line steroid therapy who exhibit one of the following responses: disease progression after 3 days, failure to achieve a PR after 7 days, failure to achieve CR after 14 days of steroid treatment (categorized as steroid resistance), or reactivation of aGVHD during tapering of steroids (categorized as steroid dependence).iii.Patients are able to be treated with the trial drug within 3 days after enrollmentiv.Prior to the trial, the subject or his or her legal representative (for subjects < 18 years of age) is capable of providing written informed consent

The exclusion criteria are as follows:i.Patients with lung disease judged by the investigator to be unfit to participate in the trial.ii.Serologically positive for HCV-Ab, TP-Ab, and HIV-Abiii.Patients with sinusoidal obstruction syndromeiv.Patients showed mental status changes due to brain lesions or other medical causes since the onset of aGVHDv.Patients with cytomegalovirus (CMV) enterocolitis, diarrhea due to transplant-associated thrombotic microangiopathy, or gastrointestinal infectionvi.Patient creatinine clearance < 30 mL/min, calculated by the Cockcroft-Gault formulationvii.ECOG score > 3viii.Patients with evidence of life-threatening complications within 6 months prior to enrollment that would interfere with the outcome evaluation of the study, including but not limited to uncontrolled infection, pulmonary hypertension, severe cardiac failure (NYHA class III and IV), unstable angina or acute myocardial infarction, and refractory hypertensionix.Patients with active malignant solid tumors within 5 years prior to the study, except for radically treated cervical cancer, in situ limited prostate cancer and nonmelanoma skin cancerx.Patients with mental or neurological disordersxi.Patients who received systemic first-line treatment other than glucocorticoids for aGVHD prior to screeningxii.Patients with a history of severe allergy to blood products or a history of allergy to allogeneic proteinsxiii.Female patients who are lactating or planning a pregnancy or egg donation during the study and the follow-up period or male patients who have plan to father a child or donate sperm during the study and the follow-up periodxiv.Participation in other clinical trials within the previous 1 month

### Investigational product

hUC-MSC PLEB001 comprises human umbilical cord-derived mesenchymal stem cells that have been ex vivo cultured and formulated in saline supplemented with human serum albumin. Saline will be used as the placebo and provided in the same packaging form as hUC-MSC PLEB001.

The investigational product will be administered by peripheral intravenous drip as follows: according to the transfusion routine, a peripheral intravenous drip, using a disposable blood transfusion set, will be conducted for investigational product administration. The initial 10 ml will be dripped at approximately 2 ml/min, and the residual volume will be dripped at 4 ml/min. After the infusion, the pipeline will be flushed with saline.

### Randomization and double-blind design

To reduce the possible selection bias and efficacy evaluation bias from investigators and subjects, this trial will adopt a randomized, double-blind, placebo-controlled design. Since the baseline treatment is the current standard treatment regimen, this study will adopt a loading design, which meets the ethical requirements.

The multicenter subblock randomization method will be used, and a random number table will be generated by professional statisticians using SAS (version 9.4) software. The subjects will be randomly allocated, and the investigational drugs will be allocated in the Central Randomization System of Clinical Information Management System (CIMS-CRS).

After signing the informed consent form, each subject will be given a screening number. The length of the screening number is N, and the naming rule is “S” + center number (XX) + sequence number (XXX). The random number is obtained after successful randomization, the length of the random number is N, and the naming rule is N-digit natural number (XXX).

In this trial, CIMS-CRS will be connected with the Alibaba Health precision traceability system to complete drug blinding. The unique tracking numbers for investigational drug distribution are generated by the drug management module of the Alibaba Health precision traceability system. The two systems work together to accurately manage and fully trace investigational drugs and clinical data.

A unique traceability code on the subject’s medication bag must be recorded using a code scanner prior to use of all medications. Normally, blinding should not be broken until all subjects have completed the study and the database is locked. To ensure the double-blind design, a light-protected infusion set will be used to shield the investigational product.

If severe safety issues arise in the study that requires the investigator to know the subject’s group, an unblinding procedure should be initiated. An emergency unblinding license will be generated in the center system, which permits the investigators and subjects to check their grouping. Immediately upon unblinding, the sponsor and the contract research organization need to be notified. Information about unblinding should be recorded in the subject’s source documentation and electronic medical record.

### Safety reporting

#### AE

Adverse events are collected through interrogation, physical examination, laboratory or other tests, and self-reporting. Investigators are required to collect AEs from the time of the first dose and continue to collect AEs until 180 days after the first infusion, death, or early withdrawal from the clinical study (whichever occurs first).

In this trial, the severity of adverse events is graded according to the common terminology criteria adverse events (CTCAE 5.0) published by the National Cancer Institute (NCI) [20]. The potential association between adverse events and investigational product will be examined based on the “Adverse Drug Reaction Reporting and Detection Workbook” issued by the National Adverse Drug Reaction Monitoring Centre.

#### SAE

The collection and assessment of serious adverse events will be consistent with the procedures for adverse events. To ensure patient safety, every SAE, regardless of suspected causality, that occurs after the patient provides informed consent and until the end of treatment visit, will be reported to the sponsor and ethics committee within 24 h of learning of its occurrence.

Some events requiring hospitalization or prolonged hospitalization may not be treated as SAEs, including hospitalization or prolonged hospitalization for reasons other than AEs and hospitalization for a surgery scheduled prior to the trial, but these must be clearly documented in the medical record.

